## Abstract

**Background:**

Some patients with depression do not respond to first and second line conventional antidepressants and are therefore characterised as suffering from treatment refractory depression (TRD). On-going psychosocial stress and dysfunction of the hypothalamic-pituitary-adrenal axis are both associated with an attenuated clinical response to antidepressants. Preclinical data shows that co-administration of corticosteroids leads to a reduction in the ability of selective serotonin reuptake inhibitors to increase forebrain 5-hydroxytryptamine, while co-administration of antiglucocorticoids has the opposite effect. A Cochrane review suggests that antiglucocorticoid augmentation of antidepressants may be effective in treating TRD and includes a pilot study of the cortisol synthesis inhibitor, metyrapone. The Antiglucocorticoid augmentation of anti-Depressants in Depression (The ADD Study) is a multicentre randomised placebo controlled trial of metyrapone augmentation of serotonergic antidepressants in a large population of patients with TRD in the UK National Health Service.

**Methods/design:**

Patients with moderate to severe treatment refractory Major Depression aged 18 to 65 will be randomised to metyrapone 500 mg twice daily or placebo for three weeks, in addition to on-going conventional serotonergic antidepressants. The primary outcome will be improvement in Montgomery-Åsberg Depression Rating Scale score five weeks after randomisation (i.e. two weeks after trial medication discontinuation). Secondary outcomes will include the degree of persistence of treatment effect for up to 6 months, improvements in quality of life and also safety and tolerability of metyrapone. The ADD Study will also include a range of sub-studies investigating the potential mechanism of action of metyrapone.

**Discussion:**

Strengths of the ADD study include broad inclusion criteria meaning that the sample will be representative of patients with TRD treated within the UK National Health Service, longer follow up, which to our knowledge is longer than any previous study of antiglucocorticoid treatments in depression, and the range of mechanistic investigations being carried out. The data set acquired will be a rich resource for a range of research questions relating to both refractory depression and the use of antiglucocorticoid treatments.

**Trial registration:**

Current Controlled Trials: ISRCTN45338259; EudraCT Number: 2009-015165-31.

## Background

Depression is a common disorder, affecting some 10% of the population [1]. It is rated by the Disease Control Priorities Project as one of the leading medical contributors to the global burden of disease [2]. It can become long-lasting and may recur frequently. Depression has a large negative impact on the quality of life of service users and their carers. It is associated with high morbidity (depression has been identified as one of the leading causes of work days lost and working-age adults receiving disability payments in the UK) [3] and mortality, through suicide and increased deaths from cardiovascular disease [4]. Clinical guidelines recommend the use of antidepressant medication for the treatment of a moderate to severe depressive episode [1,5]. Antidepressant drugs have established efficacy versus placebo in clinical trials, however, in naturalistic settings many patients have unsatisfactory outcomes. The large pragmatic STAR*D study conducted in the USA showed that even with protocol driven treatment, first line therapy with a selective serotonin reuptake inhibitor (SSRI: citalopram) in over 2500 patients was associated with remission in only 28%, and response (defined as a 50% decrease in symptom scores) in less than 50% of patients [6]. Further, second line treatment in the STAR*D study with an alternative antidepressant was associated with an even lower remission rate of 20-25% [7]. Much of the burden is consequent upon this treatment refractory depression (TRD).

Clinical response to antidepressant treatment may be influenced by a number of factors, but an inadequate neurochemical response is one likely mechanism of non-response. The majority of antidepressants, on chronic administration, elevate forebrain levels of 5-hydroxytryptamine (serotonin, 5-HT). The clinical importance of this is supported by the fact that acute depletion of tryptophan (the precursor of 5-HT) can lead to the rapid return of depressive symptoms in patients treated with antidepressants [8,9]. There is a long-held notion that life events and lack of social support predict worse treatment outcomes in patients with depression [10]. The mechanism of this may relate to the hypothalamic-pituitary-adrenal (HPA) axis. It is well established from animal and human studies that glucocorticoids influence multiple aspects of 5-HT neurotransmission (including the sensitivity of 5-HT_1A_ autoreceptors and postsynaptic 5-HT receptor efficacy [11-14] that are postulated to be central to the antidepressant mechanism of action [15]). Furthermore, dysregulation of the HPA axis can reduce the effects of antidepressants in the frontal cortex. Implantation of corticosteroid releasing pellets in rodents to induce an HPA axis dysregulation has been shown to attenuate the ability of antidepressants to elevate forebrain 5-HT levels [16]. Interestingly, there is also increasing evidence that antiglucocorticoid treatments have the opposite effect by enhancing the forebrain 5-HT response to antidepressants [17]. This suggests that reducing normal physiological levels of glucocorticoid receptor activation can increase the elevation of 5-HT in response to SSRIs. These data suggest a potential mechanism by which antiglucocorticoid strategies can enhance the clinical effectiveness of antidepressants in clinical practice.

HPA axis abnormalities are often demonstrated in patients with mood disorders. HPA axis dysregulation in depression is often characterised, particularly in those with melancholic symptoms, by a flattened cortisol diurnal rhythm with elevated trough levels of cortisol [18] and by attenuated negative feedback effects of corticosteroids on adrenocorticotrophin hormone (ACTH) and cortisol release [19]. There is increasing evidence that shows such dysregulation is associated with poor prognosis, including non-response to antidepressants and future relapse [20-26]. Further, a Cochrane review demonstrated the efficacy of antiglucocorticoid augmentation of antidepressants in patients with depression with the largest effect size seen with metyrapone [27], a cortisol synthesis inhibitor which crosses the blood–brain barrier. There have been several open or open-label, including randomised, studies of metyrapone augmentation of antidepressants, showing efficacy in treatment-resistant depression [28-32]. In addition a successful proof-of-concept double blind, placebo controlled randomised study has been conducted by Jahn and colleagues [33] in a centre in Germany, with 63 depressed inpatients. Patients were all on a serotonergic antidepressant and were randomised to add-on treatment with metyrapone (1 g/day for 3 weeks) or placebo. The primary outcome measure was the percentage of responders (defined by a set improvement on the Hamilton depression rating scale) 5 weeks after randomisation (i.e. 2 weeks after cessation of metyrapone or placebo augmentation). Patients receiving metyrapone were significantly more likely to respond than those receiving placebo, with an effect size of d = 0.63. Kaplan-Meier analysis revealed a faster response with metyrapone, which was well tolerated and without serious side-effects.

### Aims

The primary aim of the “**A**ntiglucocorticoid augmentation of anti-**D**epressants in **D**epression” (**ADD**) study is to examine the efficacy and safety of metyrapone augmentation of serotonergic antidepressants in a randomised controlled trial (RCT) in patients with Major Depression who have not responded to at least two courses of antidepressants in their current episode. The study extends research in this area by exploring the translatability of the proof of concept study described above [33] to an outpatient, primary and secondary care, UK National Health Service (NHS) population. To date, all published studies of the use of antiglucocorticoids in patients with TRD have used short treatment periods of 1-3 weeks [27], which can appear counter-intuitive in such a potentially chronic condition. However, evidence suggests that the clinical effects of antiglucocorticoids on HPA axis function persist after their prescription has ceased [34,35]. The persistence of effects on depressive symptoms and quality of life will therefore be examined in the ADD study for around 6 months after stopping metyrapone treatment compared with the 2 week follow-up period of Jahn and colleagues [33].

The exact mechanism by which metyrapone may enhance antidepressant efficacy is unknown. A secondary aim of the ADD study is to explore the impact of metyrapone on HPA axis function and the hypothesis that metyrapone leads to altered neural responsiveness to glucocorticoids with an increase in the frontocortical 5-HT response to antidepressants. In addition, a number of studies in sub-samples, drawn from the main RCT population, will also be undertaken using electroencephalographic (EEG) and functional magnetic resonance imaging (fMRI) techniques, assessment of neuropsychological function, and genetic variability to address this mechanistic aim. Only the elements of the study relating to the full RCT sample (efficacy and safety measures and HPA axis function) will be described in detail here. The sub-studies are, however, detailed in Table 1. The description of the protocol below is consistent with the SPIRIT (Standard Protocol Items: Recommendations for Interventional Trials) 2013 recommendations (see http://www.spirit-statement.org/spirit-statement/).

**Table 1 T1:** Sub-studies: data collected and rationale

**Sub- study**	**Data collected**	**Rationale**	**Participants**
Neuropsychological function	CANTAB spatial working memory (SWM) task [36].	The neuropsychological tasks have chosen on the basis of their known sensitivity to cortisol and/or 5-HT manipulations. For example SWM has been shown to be sensitive to corticosteroid manipulations in healthy controls and patients [37-39]. The FEERT, ECMT and affective go/no-go tasks, on the other hand have strong evidence for sensitivity to 5-HT manipulations [40-42], while episodic verbal memory, as tested with the VTL) is sensitive to both corticosteroid and 5-HT manipulations [43-45]. Changes in performance of the tasks following metyrapone treatment will help identify whether any improvements with the treatment may be associated with changes in HPA axis function and/or 5-HT neurotransmission.	80 patients, equal numbers from each treatment arm. 50 patients recruited in Newcastle and 30 in Manchester.
*Patients – week 0 and 5*	Verbal Learning Test (VTL) comprising neutral, positive and negative emotional words with immediate and delayed recall and recognition trails.		
*Healthy Controls – week 0*			
			55 healthy controls.
	Object-Location Memory (OLM) paradigm [46].		
	Digit Span – forward and backward.		
	Attentional Network Test (ANT) [47].		
	Facial Emotional Expression Recognition Test (FEERT) [48].		
	Emotional Categorisation and Memory test (ECMT) [48].		
	Affective Go/No Go Task [49].		
EEG: Treatment response prediction	Alpha power.	This sub-study will utilise a range of EEG variables with an evidence base for predicting response to monoaminergic antidepressants [50]. The LDAEPs have been shown to differentially predict response to serotonergic versus noradrenergic antidepressants [51]. We predict that the relationship between clinical response and LDAEP measurement will be consistent with serotonergic enhancement by metyrapone.	50 patients, equal numbers from each treatment arm, recruited in Newcastle.
	Alpha hemispheric asymmetry.		
*Patients – week 0 and 5*			
	Theta power localised to anterior cingulate.		
*Healthy Controls – week 0*			25 healthy controls.
	Loudness dependency of auditory evoked potentials (LDAEPs).		
EEG: Neural correlates of emotional processing and memory	Emotional source memory task (ESMT) [52].	The ESMT task will examine the neural correlates of emotional episodic memory in patients and the effects of metyrapone treatment. This will supplement the information provided in the VTL in the neuropsychological sub-study described above.	50 patients, equal numbers from each treatment arm, recruited in Newcastle.
	Putative EEG measure of long-term potentiation (LTP) [55].		
			25 healthy controls.
		The putative LTP measure has previously been shown to be impaired in depressed patients [53] and LTP is known to be sensitive to corticosteroids in animals [54]. We predict that treatment with metyrapone will normalise potential impairments in this measure in the patient cohort.	
*Patients – week 0 and 5*			
*Healthy Controls – week 0*			
Newcastle fMRI sub-study	Facial emotional processing task (FEPT) [56].	FEPT allows investigation of a functional cortical network involved in the processing of emotions and emotional responses. It supplements information obtained using the FEERT in the neuropsychological sub-study described above and enable localisation of any effects seen. Likewise the EEMET will supplement the information provided in the VTL.	30 patients from NE Hub - equal number from each treatment arm.
*Patients – week 0 and 5*			
	Emotional episodic memory encoding task (EEMET) [57].		
*Healthy Controls – week 0*			15 healthy controls matched for age, handedness and IQ.
Manchester fMRI sub-study	Neural correlates of episodic and working memory.	The episodic memory task will involve encoding and recall of neutral and emotionally valenced pictures, while the working memory task will utilise the N-back task. This will further supplement the data obtained in the neuropsychological sub-study.	30 patients from NW Hub - equal number from each treatment arm.
*Patients – week 0 and 5*			
	Hydrocortisone pharmacoMRI [58].		
			30 healthy matched controls.
		For the pharmacoMRI, at week 0 patients receiving metyrapone will receive a 100 mg hydrocortisone bolus and those receiving placebo saline. Healthy controls will be randomised to hydrocortisone or saline. At week 5 all patients will receive hydrocortisone. We predict that blunted acute hippocampal responses to hydrocortisone pre-treatment will normalise after metyrapone, but not placebo, treatment.	
*Healthy Controls – week 0*			
Genotyping		We will look for an association between treatment outcome, its predictors and genetic polymorphisms and also for genetic influences on brain information processing (for example brain derived neurotropic factor (BDNF) and corticotrophin releasing factor (CRF) variants and hippocampal response to hydrocortisone in Manchester/amygdala response to emotional faces in Newcastle). We will also investigate the DNA samples for rare genetic variants (e.g. copy number variations). We will determine our candidate gene list based on previous candidate gene association studies and recent novel findings from genome-wide association studies with major depressive disorder and by considering relevant genes for the function of the HPA axis.	All patients and healthy controls approached for specific consent to provide a DNA sample.
*Patients and Controls*			

Note, all the patients will be recruited from the main ADD study RCT with additional inclusion criteria of being aged 18-60. To assist in interpretation of the data an additional cohort of healthy controls will be recruited who are currently psychiatrically well, confirmed through SCID interview and HDRS17 < 5 and being on no current psychotropic medication. Exclusion will also include presence of a past history of psychiatric illness or a history of psychiatric illness in a first degree relative. The controls will be matched with the patients for age (+/- 5 years), gender, handedness and IQ (+/- 7 points as assessed using the National Adult Reading Test [59]). Handedness will be assessed for all subjects taking part in EEG and fMRI studies (using the Edinburgh Handedness Inventory [60]). Only right handed patients and healthy controls will be included in the fMRI sub-studies described below.

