### Intervention

Participants will continue their existing antidepressant regime. Randomisation will be in a 1:1 ratio of metyrapone to matched placebo using permuted block randomisation, stratified by inclusion in mechanistic studies sub-sample, level of care setting (i.e. primary or secondary care) and by centre. A randomisation code will be computer generated by the Newcastle Clinical Trials Unit and coded packs of the study drug and matched placebo will be produced, according to the randomisation schedule. All medication will be supplied from a single central pharmacy with all participants and study staff blinded to treatment allocation. To ensure blinding the metyrapone will be over-encapsulated and the placebo will be visually identical. Participants in the treatment arm will receive study drug (metyrapone 500 mg or placebo) twice daily, prescribed in the morning and at noon, for 21 days. Adherence to medication will be assessed using measures of 11-deoxycortisol as described below under “HPA axis Assessment”.

Apart from treatment with the experimental intervention, all other treatments will remain under the control of the patient’s normal treating psychiatrist and/or general practitioner. However, the patients’ clinicians will be encouraged to avoid changes to medications between enrolment (week -2) and the primary outcome time point (week +5) unless there is a compelling clinical reason to alter treatment. All current medication will be recorded at all follow up time points.

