### HPA axis assessment

Cortisol levels to determine the cortisol awakening response (CAR) [80] will be obtained at the start of treatment (week 0) and then again at +3 and +5 weeks for all patients. This entails participants collecting 5 ml of saliva by passive drool [81] into a plastic collecting tube on wakening and then again at 15 minute intervals for a further hour. A total of five samples will be collected on each occasion either the day before or day after the planned study visit. Participants will also be asked to collect a saliva sample for cortisol assay at 11 pm the night before each of the three CAR assessments. In addition to collection of saliva samples, participants will complete a brief questionnaire relating to the nature and quality of sleep the night before the CAR assessment.

In addition to the saliva samples, serum samples will be taken at -2, +1 and +5 weeks for analysis of cortisol precursors and metabolites. Metyrapone administration has previously been shown to cause an increase in levels of ACTH, DHEA and 11-deoxycortisol together with an increase in the cortisone:cortisol ratio [33,82]. The increase in 11-deoxycortisol between weeks -2 and +1 will be used as a measure of adherence to medication since this has been shown to be highly sensitive to treatment with metyrapone [33,82].

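### Manchester pharmacoMRI sub-study: the week-0 challenge is set by trial arm, so the predicted between-arm difference in change of hydrocortisone response cannot be estimated

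*Protocol article*

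**What the plan says.** The Manchester fMRI row of Table 1 (protocol article, Aims) sets the pharmacoMRI challenge for trial patients by their treatment arm: "at week 0 patients receiving metyrapone will receive a 100 mg hydrocortisone bolus and those receiving placebo saline". The second scan is uniform: "At week 5 all patients will receive hydrocortisone". The controls are handled differently: "Healthy controls will be randomised to hydrocortisone or saline". The row then gives its hypothesis: "We predict that blunted acute hippocampal responses to hydrocortisone pre-treatment will normalise after metyrapone, but not placebo, treatment".

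The sub-study takes "30 patients from NW Hub - equal number from each treatment arm", and the note below Table 1 says that "all the patients will be recruited from the main ADD study RCT". These patients therefore count in the primary comparison.

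Three other sections bear on this:

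- Intervention describes the trial as conducted "with all participants and study staff blinded to treatment allocation", and makes membership of the mechanistic sub-sample a stratification factor.
- Randomisation visit (week 0) has trial medication starting the day after that visit, so the week-0 challenge precedes any metyrapone.
- HPA axis assessment allows the cortisol awakening response (CAR) saliva to be taken "either the day before or day after the planned study visit", with the 11 pm sample on the night before the CAR.

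**The concern.** The prediction is an arm-by-time statement: the response to hydrocortisone should change in one arm and not in the other. To estimate it, both arms need a hydrocortisone response before and after treatment. Under the stated rule the placebo arm goes from saline to hydrocortisone while the metyrapone arm goes from hydrocortisone to hydrocortisone. A larger sample or a different model cannot supply the missing scans, and neither can an analysis plan.

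Two side effects follow within this subset. Challenge and arm carry the same information, which sits awkwardly with the blinding statement. And if saliva is collected after the visit, the baseline HPA measures may follow a glucocorticoid bolus in one arm only. Those baselines feed the mechanistic objectives for the full sample, including whether baseline HPA function predicts response.

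**Working it through.** **Main-trial figures first** (Sample size section: difference 6, SD 12, alpha 0.05, taken as two-sided because that reproduces the figures). n = 2(1.960 + 0.842)² × (12/6)² = 62.8, so 63 per group; 63/(1 − 0.10) = 70. At 90% power the same formula gives 85, and 85/0.90 rounds up to 95. All agree with the article. The sub-study has no stated power figure.

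**What the scans can estimate.** Write μ(arm, week, challenge), with M = metyrapone, P = placebo, H = hydrocortisone, S = saline.

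| | Week 0 | Week 5 |
|---|---|---|
| Metyrapone (15) | μ(M,0,H) | μ(M,5,H) |
| Placebo (15) | μ(P,0,S) | μ(P,5,H) |

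- Predicted contrast: [μ(M,5,H) − μ(M,0,H)] − [μ(P,5,H) − μ(P,0,H)]. The cell μ(P,0,H) is empty: 0 of 15 placebo patients. Neither the placebo change nor the difference in change is estimable. With an intercept, arm and week-0 challenge have rank 2 of 3, so they are fully aliased.
- Change within metyrapone, μ(M,5,H) − μ(M,0,H): estimable, but with no concurrent control for time, repeat scanning or repeat exposure.
- Week-0 contrast, μ(M,0,H) − μ(P,0,S): estimable, randomised and pre-treatment, and it parallels the contrast in controls.
- Week-5 contrast, μ(M,5,H) − μ(P,5,H): estimable and randomised. It equals the treatment effect plus any effect of a second rather than a first hydrocortisone exposure.

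If the challenge were allocated independently of arm, the placebo change and the difference in change would both become estimable.

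**Precision** (normal approximation, 80% power, two-sided 0.05; detectable standardised difference = 2.802 × √(2/n)). With 15 per arm: 2.802 × √(2/15) = 1.02. With 7.5 per arm, the average number having hydrocortisone at both visits under a crossed list: 2.802 × √(2/7.5) = 1.45.

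**Reach into the main trial.** The bolus goes to 15/70 = 21.4% of the metyrapone arm and 0/70 of the placebo arm. Over 140 patients, arm and bolus correlate at 0.35 but are not aliased (rank 3 of 3). If the bolus moved week-5 MADRS by d points, the primary difference would shift by 0.214 × d. The documents give no d, so the values below are assumptions. Power is for 63 per group with the bias working against metyrapone.

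| Assumed d | Shift in difference | Power |
|---|---|---|
| 0 | 0 | 80% |
| 1 | 0.21 | 77% |
| 2 | 0.43 | 74% |
| 3 | 0.64 | 71% |
| 6 | 1.29 | 60% |

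A 1-point shift needs d = 70/15 = 4.7 points, still present five weeks after a single bolus.

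**Sensitivity analysis without these patients.** This leaves between 63 − 15 = 48 and 70 − 15 = 55 per arm, with power of about 69% to 75% for a 6-point difference.

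**Saliva timing.** If the CAR is taken the morning after the week-0 visit, the 11 pm sample falls on the evening of the visit. If the scan is on the visit day (an assumption), both samples follow the challenge: hydrocortisone in the metyrapone arm, saline in the placebo arm.

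**The case against.** The strongest reply is that randomisation does much of the work. Before treatment the arms are alike in expectation, so the metyrapone arm's week-0 hydrocortisone response can stand in for the missing placebo one, and the week-5 comparison addresses the prediction directly. The layout also gives a 15 versus 15 hydrocortisone/saline contrast in patients at week 0, matching the one in controls. This stands in part: a reader might infer that the prediction is wholly untestable, and it is not. But the substitution leaves only the week-5 comparison, in which one arm is on its second exposure and the other on its first. The article does not mention that assumption.

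A reader might also infer that hydrocortisone is confounded with metyrapone in the trial as a whole. The documents do not support that. It is one bolus before the first trial dose, in at most 15 of 70 patients, and the main effect remains estimable. The upper values of d in the table have no basis in the article; d = 6 equals the whole target difference.

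Nor is unblinding shown. The challenge could be supplied in coded form, and a journal article may leave that to the full protocol. What stands is that decoding the challenge, for scan analysis or for any other reason, would disclose the arm.

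The saliva point is conditional too, since collection the day before is equally allowed.

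**Conclusion.** The concern holds for the sub-study and should be fixed; it does not put the primary analysis in doubt. As written, neither the placebo-arm change in hydrocortisone response nor the predicted between-arm difference in change can be estimated. The usable randomised test is the week-5 comparison, conditional on no carry-over or order effect, and with 15 per arm it detects only a standardised difference of about 1.0 or more. The link between challenge and arm, and the possible one-arm contamination of baseline saliva, are confined to this subset. Any effect on the primary MADRS difference is a partial imbalance (21% against 0%) of unknown and probably small size.

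This rests on an equal 15/15 split with all patients scanned, and on Table 1 describing the rule accurately. If Table 1 misdescribes it, the text needs correcting rather than the design. No view is taken on the challenge agent or its dose.

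**What to change.** 1. Reconcile the Manchester row of Table 1 with the Intervention and HPA axis assessment sections.
2. Allocate the week-0 challenge independently of trial arm, for example by a coded 1:1 list crossed with arm. Compare the week-5 response by arm, with week-0 challenge in the model. This keeps the 15 versus 15 contrasts at both visits and balances exposure order between arms. The controls' challenge is already randomised, so the method is familiar to the study.
3. In these patients, collect week-0 CAR and 11 pm saliva before the challenge.
4. Add a sensitivity analysis of the primary outcome without the pharmacoMRI patients.
5. For patients already scanned under the current rule, name the week-5 comparison as the test, state its no-order-effect assumption, and do not claim a between-arm difference in change.

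The administrative cost is a new allocation list and a short amendment. The statistical cost is larger: only 7 or 8 patients per arm would have hydrocortisone at both visits, so the change contrast would be imprecise (detectable difference about 1.45 SD). Recruitment began in February 2011 and the article does not say how many patients had been scanned. A mid-study switch would mix two allocation rules within 30 patients, so the analysis would have to identify which rule applied to each.
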